### Adverse events comprising the following individual outcomes: (a) the proportion of patients with systemic embolism or 'total stroke', (b) major bleeding, (c) minor bleeding, and (d) any bleeding event recorded during the 12-month follow-up period

(a) Systemic embolism and total stroke rates have been used in studies evaluating antithrombotic medications. Applying standard definitions [6,8], we consider total stroke as comprising ischaemic stroke and haemorrhagic cerebral events (intracerebral, intracranial and subarachnoid haemorrhages, and subdural haematoma) and stroke not otherwise specified as either haemorrhagic or ischaemic. Haemorrhagic stroke will include traumatic and nontraumatic intracranial haemorrhage, subarachnoid haemorrhage, and subdural haematoma. This is in keeping with definitions applied in previous trials and systematic reviews of randomised controlled trials of antithrombotic treatment in atrial fibrillation [6,8]. We will also consider systemic embolism, haemorrhagic stroke, ischaemic stroke, and stroke not otherwise specified as four individual outcomes. TIA will comprise a separate cerebrovascular outcome and not be included in the composite outcome, in keeping with previous definitions of total stroke [6,8]. The likely rarity of these events, however, may preclude robust statistical analysis for these individual outcomes.

(b) A major bleeding event is defined as a haemorrhagic stroke or other bleeding associated with a hospital admission or blood transfusion. All other bleeding events will be classified as (c) minor bleeding, including anaemia and bruising. Our classifications of major and minor bleeding correspond with definitions used elsewhere [6,8]. We will also compare groups on the occurrence of (d) *any *bleeding event, in recognition that this outcome will likely involve a greater number of events, permitting a more robust statistical analysis and also minimising the effect that misclassification will have on our definitions of major and minor bleeding events.

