## Cerebrovascular and bleeding events

All entries of cerebrovascular and bleeding events or episodes noted in the medical record from January 1, 2004 will be recorded so that the history of these events current at the time of randomisation and new events occurring during the 12 months after the date of randomisation will be recorded (see below).

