### Losses to follow-up

Patients identified as having atrial fibrillation without any recorded contact with GPs during the follow-up period will be considered lost to follow-up. The proportion of patients lost to follow-up or with partly completed follow-up will be compared across groups.

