As practices (clusters) were randomised, we needed to allow for the correlation between the outcomes of patients from the same cluster. We have inflated the sample-size estimate by the design effect (DEFF); DEFF = [1 + (*m *- 1)ρ], where *m *is the average number of patients per cluster and ρ is the intracluster correlation coefficient (ICC) that quantifies the amount of within-cluster correlation for the outcome of interest [37]. An estimate for the ICC for warfarin uptake in patients with atrial fibrillation recruited within general practice clusters is 0.029 [11]. We have conservatively chosen an ICC of 0.04 in recognition of the imprecision with which ρ is estimated. We estimate an average of 20 eligible patients with NVAF per GP will be identified. This estimate assumes an average of 350 eligible patients over the age of 65 per GP, a prevalence rate for NVAF in general practice of ~8.6% [38], that our computerised search strategy will identify 85% of patients with atrial fibrillation, and that 80% of patients will not refuse permission for an independent medical record audit. Based on previous experience of recruiting GPs [39], we expect to recruit an average of 1.25 GPs per practice, yielding an average sample size of 25 patients per practice (1.25 × 20). The estimated DEFF is 1.96 (*i.e*., [1 + (25 - 1)0.04]). Therefore, we require 798 patients per group (*i.e*., 407 × 1.96). Assuming 10% will die, move away during the study, or be lost to follow-up, our revised sample size is 887 per group. We therefore aimed to recruit 36 practices per group (*i.e*., 887 ÷ 25 patients per practice), 72 practices in total, and 90 GPs in total (72 × 1.25 GPs per practice). To further allow for 10% drop out at practice level, we aimed to recruit 40 practices per group (80 in total, or 100 GPs), yielding a total patient sample of 2,000 (100 GPs × 20 patients or 80 practices × 25 patients) or 1,000 per group.

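### The major-bleeding definition has no fatal criterion, so a recorded fatal extracranial bleed with neither admission nor transfusion is scored as minor

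*Protocol article*

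**What the plan says.** The adverse-events part of Secondary outcomes sets a two-class rule. The upper class is: "A major bleeding event is defined as a haemorrhagic stroke or other bleeding associated with a hospital admission or blood transfusion". The lower class takes everything else: "All other bleeding events will be classified as (c) minor bleeding, including anaemia and bruising". For the stroke route the scope is wide: "Haemorrhagic stroke will include traumatic and nontraumatic intracranial haemorrhage, subarachnoid haemorrhage, and subdural haematoma". The same section adds outcome (d), any bleeding event, partly for the purpose of "minimising the effect that misclassification will have on our definitions of major and minor bleeding events".

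Three other sections bear on the point:

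- *Cerebrovascular and bleeding events* governs capture: "All entries of cerebrovascular and bleeding events or episodes noted in the medical record from January 1, 2004 will be recorded".
- *Losses to follow-up* defines a lost patient: "Patients identified as having atrial fibrillation without any recorded contact with GPs during the follow-up period will be considered lost to follow-up". It makes no exception for a patient known to have died.
- *Sample size* names death and loss as separate items: "Assuming 10% will die, move away during the study, or be lost to follow-up".

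**The concern.** The two bleeding classes are exhaustive. A bleed that fails the major rule is minor, with no third class and no room for judgement. The rule uses admission and transfusion as markers of severity, and these fail for a patient who dies before either can happen. The most severe extracranial bleed can then be counted with bruises.

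This matters because the intervention aims to raise anticoagulant use, and major bleeding is the listed outcome that would show serious extracranial harm from doing so. Death is not one of outcomes (a) to (d), so no mortality comparison among them would recover the event.

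A smaller point concerns patients who die early in the year. One who dies before any GP contact after randomisation meets the written definition of lost, although the sample-size section treats death and loss as different things.

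**Working it through.** **No stated figure depends on this rule.** The sample size rests on the primary outcome only. For 60% against 50%, two-sided 5% (sidedness assumed) and 80% power, the standard formula gives 388 per group without and 408 with continuity correction. The second agrees with the article's 407 to within one patient. The later steps also reproduce: 1 + (25 − 1) × 0.04 = 1.96; 407 × 1.96 = 797.7, so 798; 798 ÷ 0.9 = 886.7, so 887. None of these changes.

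**Applying the rule to cases.**

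| Recorded event | Haemorrhagic stroke? | Admission or transfusion? | Class as written |
|---|---|---|---|
| Fatal subdural haematoma at home | Yes | No | Major |
| Gastrointestinal bleed, admitted, survives | No | Yes | Major |
| Fatal gastrointestinal bleed at home | No | No | Minor |
| Bruising | No | No | Minor |

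The third row is the defect. The first row shows that it is limited to extracranial bleeds, because intracranial bleeds are major by definition.

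**Scale (illustration).** Inputs: 1.9% and 2.0% major haemorrhage per year in the two arms of the elderly primary-care trial described in Background; 1,000 patients per group, the recruitment target in Sample size; 12 months of follow-up.

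- Expected major bleeds per group: 1,000 × 0.019 = 19 and 1,000 × 0.020 = 20.
- Share that is fatal, extracranial and without admission or transfusion: not in the article; assumed 1% to 20%.
- Events moved from (b) to (c): 19 × 0.01 = 0.19 at the low end and 20 × 0.20 = 4.0 at the high end.
- With 798 patients per group: 798 × 0.019 × 0.01 = 0.15 to 798 × 0.020 × 0.20 = 3.2.
- Change in the count of *any*-bleeding events: zero.

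The cited rate includes haemorrhagic strokes, which cannot be downgraded here, so the upper end is generous. If the same share were moved in both arms, the ratio of major-bleeding rates would be unchanged and the absolute difference would shrink by that share.

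**Loss to follow-up, sections side by side.** The loss definition attaches to the patient and requires no recorded GP contact in the whole 12 months. The capture rule takes every bleed noted in the record. No section says that recorded events of patients classed as lost are dropped, and none says that they are counted. The sensitivity analyses for losses concern the primary outcome only.

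**The case against.** The strongest reply is that outcome (d) already deals with misclassification. Every bleed counts there, so nothing is hidden overall. That is right about counting, but (d) pools fatal bleeds with bruising and anaemia and cannot show an excess of severe ones. Only (b) can do that.

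A second reply is that the article says its classes correspond to published definitions, and that an article condenses coding rules. Those sources and the audit form are not shown, so the correspondence cannot be checked. Condensation does not explain the gap, because the article gives a closed rule with an explicit residual class and that rule determines the result.

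A third reply is that such events are rare and that the same rule applies to both arms. This stands and limits the weight of the point.

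A reader might infer more than the text supports in three ways:

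- **That deaths before GP contact are removed from the harm outcomes.** Nothing says so. Capture covers all noted bleeds, and analysis is by intention to treat. Such patients should also be few: the cohort had attended within the previous 12 months, patients with a life expectancy under 12 months were taken off the list, and the cited local guidance has warfarin patients tested at least monthly. Any count of these deaths would rest wholly on assumed rates.
- **That a death in an emergency department is certainly minor.** This depends on how admission is read and on whether blood was given. The clean case is a death outside hospital.
- **That the trial could conceal a real excess of major bleeding.** The article gives no reason to expect misclassification to differ by arm.

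**Conclusion.** The point holds in a limited form. As written, the rule scores a recorded fatal extracranial bleed with neither admission nor transfusion as minor. This follows from the wording alone and needs no outside source.

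The consequence is confined to the division between outcomes (b) and (c), both secondary. The likely size is about 0.2 to 4 events per 1,000 patients per group. That range rests on the cited trial's bleeding rate carrying over to this cohort and on the assumed 1% to 20% share. The primary outcome, the sample size and outcome (d) are unaffected.

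On loss to follow-up, only a clarification is warranted: the definition does not separate a known death from a loss, and the handling of recorded events in such patients is not stated. Adding all-cause death as an outcome would be a matter of preference, and this point does not depend on it.

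**What to change.** In the adverse-events section, give major bleeding three routes: haemorrhagic stroke, fatal bleeding at any site, and other bleeding that meets the existing admission or transfusion criterion. Minor bleeding stays as the remainder. Apply the revised rule blind to allocation, before the database is locked and group codes are released, to the bleeding entries that the audit already collects.

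As a minor companion change, state under Losses to follow-up that a patient with a recorded death is a known death and not lost, in line with the sample-size section, and that events recorded up to and including the fatal one count in outcomes (a) to (d).

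The cost is two or three sentences. Data collection has started, so if the audit form has no place for date and cause of death, some records may have to be reopened. Cause of death will be missing for some patients; the number should be reported by arm.

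The trial conclusions do not hang on this, but it is a cheap correction to a named safety outcome.

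### Anaemia counts as minor bleeding, and so as any bleeding, without having to be due to blood loss or clearly new since randomisation

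*Protocol article*

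**What the plan says.** All the text is in the protocol article.

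- **Major bleeding (secondary outcomes, adverse events, item b):** "A major bleeding event is defined as a haemorrhagic stroke or other bleeding associated with a hospital admission or blood transfusion".
- **Minor bleeding (item c):** "All other bleeding events will be classified as (c) minor bleeding, including anaemia and bruising". No cause, haemoglobin threshold or onset date is attached to anaemia.
- **Any bleeding (item d):** this pools (b) and (c). The outcome heading sets its window as "any bleeding event recorded during the 12-month follow-up period". Two reasons are given for it. One is "in recognition that this outcome will likely involve a greater number of events, permitting a more robust statistical analysis". The other is "minimising the effect that misclassification will have on our definitions of major and minor bleeding events".
- **Data collection (section on cerebrovascular and bleeding events):** "All entries of cerebrovascular and bleeding events or episodes noted in the medical record from January 1, 2004 will be recorded". The stated purpose is to establish both the history at randomisation and the "new events occurring during the 12 months after the date of randomisation will be recorded".

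The adverse-events section adds that its major and minor classes match definitions used in cited work. That cannot be checked from the documents.

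**The concern.** A bleed is an event with a date. Anaemia is a state that can last for years, has many causes besides bleeding, and can be noted again at any consultation. The definition names it as a form of minor bleeding and gives the analyst no rule for separating anaemia caused by blood loss from other anaemia, or new anaemia from old.

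Patients with unrelated anaemia would be counted in both arms whatever the intervention does. They add events to (c) and (d) but no information about treatment, and they draw the comparison towards no difference. The case for (d) rests partly on its larger event count, but extra events of this kind weaken a comparison.

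What is at stake is the safety reading. The trial tries to raise anticoagulant use in patients over 65, and the Background reports that GPs hold back from prescribing when they perceive a risk of even minor bleeding. A finding of similar any-bleeding rates would speak directly to that worry, so it should not be reassuring merely because unrelated anaemia was counted in both arms.

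**Working it through.** **1. The passages side by side.**

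| Question | Data-collection section | Outcome definition |
|---|---|---|
| Must the anaemia be due to bleeding? | Refers to bleeding events or episodes; anaemia not mentioned | Anaemia named as minor bleeding; no attribution required |
| Must it be new? | Separates history from new events | Only recorded during follow-up |
| Does pooling into (d) help? | – | Removes major/minor confusion only |

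The split between history and new events works for discrete bleeds. It does not say how to code a persistent state noted both before and after randomisation. Elsewhere the article does write such rules. Atrial fibrillation first noted only after randomisation is excluded as newly diagnosed, and only comorbidities noted before randomisation enter the CHADS2 score. Anaemia has no equivalent rule.

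**2. The plan's own figures.** No rate, effect size or power is stated for any bleeding outcome, so there is no bleeding figure to reproduce. The sample size for the primary outcome (50% versus 60%, 80% power, 5% level) does reproduce:

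- Per group under individual randomisation: 388 without and 408 with continuity correction; the article says 407.
- Design effect: 1 + (25 − 1) × 0.04 = 1.96.
- 407 × 1.96 = 797.7, given as 798; 798 ÷ 0.9 = 887.

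The effective size used below is 798 ÷ 1.96 = 407 per arm. Applying the primary outcome's design effect to bleeding is an assumption.

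**3. Direction of the effect.** Let p be the true bleeding risk and a the proportion with unrelated anaemia noted in the year, equal in both arms and independent of bleeding. Then:

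- recorded risk = 1 − (1 − p)(1 − a)
- recorded risk difference = (1 − a) × true risk difference

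The difference shrinks by the factor 1 − a. The ratio shrinks further because both risks rise. The direction therefore does not depend on the rates chosen.

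**4. Illustration A.** Assumed true risks are 8% versus 10%; z = difference ÷ √{[p₁(1 − p₁) + p₂(1 − p₂)] ÷ 407}, using the recorded risks.

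| a | Recorded risks | Difference (points) | Ratio | z |
|---|---|---|---|---|
| 0 | 8.0% vs 10.0% | 2.0 | 1.25 | 1.00 |
| 5% | 12.6% vs 14.5% | 1.9 | 1.15 | 0.79 |
| 10% | 17.2% vs 19.0% | 1.8 | 1.10 | 0.67 |
| 15% | 21.8% vs 23.5% | 1.7 | 1.08 | 0.58 |

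For a = 5%: 1 − 0.92 × 0.95 = 0.126; 1 − 0.90 × 0.95 = 0.145; 0.145 ÷ 0.126 = 1.15.

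**5. Illustration B.** Assumed true risks are 10% versus 15%. Odds ratios are shown because the plan uses logistic models.

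| a | Recorded risks | Risk ratio | Odds ratio | Power |
|---|---|---|---|---|
| 0 | 10.0% vs 15.0% | 1.50 | 1.59 | 58% |
| 5% | 14.5% vs 19.25% | 1.33 | 1.41 | 44% |
| 10% | 19.0% vs 23.5% | 1.24 | 1.31 | 35% |
| 20% | 28.0% vs 32.0% | 1.14 | 1.21 | 24% |
| 30% | 37.0% vs 40.5% | 1.09 | 1.16 | 18% |

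**6. How large a true excess is plausible.** The trial is sized for a 10-point rise in anticoagulation. If the intervention changed bleeding only through that rise, a 2-point excess (A) would need 0.02 ÷ 0.10 = 20 extra bleeding patients per 100 additionally treated, and a 5-point excess (B) would need 50. With assumed risks of 5% off and 15% on anticoagulation, the arms would be 0.5 × 15 + 0.5 × 5 = 10% and 0.6 × 15 + 0.4 × 5 = 11%, a ratio of 1.10 with about 7% power before any anaemia is counted. At a = 10% the ratio is 1.05.

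**The case against.** **The text speaks of bleeding events.** A reader might infer that anaemia of any cause is counted. The documents do not say so: the sentence classifies bleeding events, and it can be read as meaning anaemia noted as a bleed. This stands. What remains is that the wording allows both readings and gives no rule for choosing.

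**New events are already distinguished.** The data-collection section does separate history from new events, so it would be wrong to say that nothing points to newness. The outcome definition does not carry the distinction through, and a recurring entry for a chronic state falls between the two.

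**Bruising.** A reader might extend the point to bruising. Bruising is bleeding into tissue and plausibly related to anticoagulation, so it belongs in the count.

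**The safety answer as a whole.** A reader might conclude that the trial's bleeding results cannot be trusted. That goes too far. Major bleeding is analysed separately and requires admission or transfusion, so it is largely unaffected. The plan also calls (d) more robust only relative to rarer outcomes, not robust outright.

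**A false excess.** More warfarin use could mean more contact and more chances to note anaemia in the intervention arm. The extra testing the article describes is INR testing, and nothing says it includes haemoglobin, so this is conjecture.

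**No conclusion is shown to change.** In illustration A the comparison is inconclusive with or without anaemia, and a smaller, more realistic excess would be hard to detect under any rule. This stands, and it limits the weight of the point.

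**Attribution brings its own bias.** GPs are not blinded and may attribute anaemia to bleeding more readily in patients on warfarin. This is a good reason not to make attribution the main definition.

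**Detail left to the full protocol.** An article may omit coding rules. Here, however, it states a rule that names anaemia, and that stated rule is what needs completing.

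**Conclusion.** The concern holds in a limited form. The definition admits anaemia to minor and any bleeding without a link to blood loss, and does not clearly exclude long-standing anaemia that is noted again. Pooling major and minor bleeding protects against confusion between those two classes and does nothing about a non-bleeding condition counted as either.

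The direction is firm if unrelated anaemia is equally common in both arms: (c) and (d) move towards no difference. The size cannot be derived, because the documents give no bleeding or anaemia rate. Under the assumed rates above, 5% to 15% unrelated anaemia takes a ratio of 1.25 to between 1.15 and 1.08, while the risk difference moves only from 2.0 to between 1.9 and 1.7 points.

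This is a worthwhile clarification of two secondary safety outcomes. It leaves the primary outcome unchanged and is not evidence that a bleeding excess will be hidden.

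**What to change.** In the adverse-events definition, add that anaemia counts in (c) and (d) only if its first entry in the audited record is dated after randomisation. The dated entries from January 2004 that the audit already collects should make this determinable.

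Report (c) and (d) both with and without anaemia. The date rule removes chronic anaemia but not new anaemia from other causes, and the paired results show how far the comparison depends on it. If the audit form captured cause, add a further version limited to anaemia that the record attributes to bleeding. No section says that cause is collected, so this version is conditional. Keep bruising in every version.

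The Discussion says data collection has begun. These are analysis rules, and they can be fixed before the group codes are released to the study statistician.

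The cost is a sentence or two and one or two extra runs. The version without anaemia has fewer events and may omit occult bleeds recorded only as anaemia. The date rule also drops patients with earlier anaemia whose later anaemia came from a bleed, unless the bleed itself was noted.

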### Subgroup analyses

For our primary outcome, we will carry out subgroup analyses, testing for interaction effects between four variables and trial arm status: (1) CHADS2 scores, (2) patient age (65 to 74 years, 75 to 84 years, and 85+ years), (3) recorded use of oral anticoagulation current at time of randomisation (that is, within three months of randomisation; yes or no), and (4) patient sex.

### Baseline comparisons between DESPATCH intervention and control groups

We will compare groups on key patient and practice characteristics current on the date of randomisation. Specifically, we will compare the DESPATCH and control groups on the numbers of patients identified with atrial fibrillation, patient sex, age (mean and median differences), CHADS2 scores (0, 1, 2+, and mean scores), use of oral anticoagulation current at time of randomisation (that is, up to three months before randomisation; yes or no), and whether patients were recruited from practices where one or more than one GP participated in the study.

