## Ascertainment of comorbidities and antithrombotic treatment

Comorbidities needed to calculate the CHADS2 score and other cerebrovascular risk factors will be noted. Nurses will search the medical record from January 1, 2004 onwards to allow ascertainment of medical history available at the time of randomisation.

Nurses will record antithrombotic treatments and dates of noted use. Dates and results of international normalised ratio (INR) testing and recorded suspensions of anticoagulation, if prescribed, are also noted. These data were collected to enable ascertainment of antithrombotic use current at randomisation and outcome assessment during the 12-month period after randomisation (see below).

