## Secondary outcomes

### The proportion of patients prescribed antithrombotic treatment judged as 'appropriate' according to stroke risk

Stroke risk will be assessed using a validated, evidence-based risk stratification scheme and evidence-based guidelines. At the time the study was initiated, the evidence-based risk stratification scheme often endorsed by national and international guidelines was the CHADS2 score [35]. Local guidelines recommend anticoagulation with warfarin for patients with a CHADS2 score of 2 or higher, aspirin or warfarin for patients with a CHADS2 score of 1, and aspirin for patients with a CHADS2 score of 0. This outcome will be measured for *any *time within 12 months of postrandomisation and for current use, as defined above. Only comorbidities noted in the medical record prior to the date of randomisation will be considered in the calculation of the CHADS2 score.

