### Statistical analysis

All outcomes will be analysed according to the intention-to-treat principle, where patients are analysed according to the arm to which their practice cluster was allocated. Analyses of the outcomes will be implemented using marginal logistic regression models using generalised estimating equations (GEEs), with information sandwich ('robust) estimates of standard error to allow for within-cluster (within-general practice) correlation for dichotomous outcomes [40]. An exchangeable correlation structure will be specified for the marginal models using GEEs. Clustering will be accounted for only at the practice level as this is the unit of randomisation. Analyses will adjust for stratification of GPs by LGA.

In addition to unadjusted analyses, we will carry out adjusted analyses to allow for the effect of characteristics, current at the time of randomisation, as noted above.

Percentage of inter- and intrarater agreement and kappa coefficients will be calculated to quantify rates of reliability for the collected audit data [41].

Significance of the study results, specifically, the effect of the intervention on primary and secondary outcomes, will be ascertained by examining the magnitude of the estimated effect of the intervention and corresponding 95% CIs. When testing for interaction terms, a *p *value of < .05 will be used to determine significance of the effect. Analyses will be carried out blinded to group allocation.

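### For the two appropriate-treatment secondary outcomes, the adjusted analyses use baseline anticoagulation, which is not the baseline value of those outcomes at CHADS2 0 or 1: precision is given up, without bias

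*Protocol article*

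**What the plan says.** In the protocol article, *Statistical analysis* first plans unadjusted models and then says: "we will carry out adjusted analyses to allow for the effect of characteristics, current at the time of randomisation, as noted above". No list is repeated there. The matching list is in *Baseline comparisons between DESPATCH intervention and control groups*. It covers numbers with atrial fibrillation, sex, age, CHADS2 ("CHADS2 scores (0, 1, 2+, and mean scores"), single- or multi-GP participation, and one treatment variable: "use of oral anticoagulation current at time of randomisation (that is, up to three months before randomisation; yes or no". It names no baseline aspirin, antiplatelet or appropriateness variable.

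The first appropriateness outcome under *Secondary outcomes* is scored by stroke risk: "Local guidelines recommend anticoagulation with warfarin for patients with a CHADS2 score of 2 or higher", then "aspirin or warfarin for patients with a CHADS2 score of 1, and aspirin for patients with a CHADS2 score of 0". The second appropriateness outcome uses the same rule and adds INR frequency and range criteria for warfarin users.

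The data for a baseline version of this score exist. *Ascertainment of comorbidities and antithrombotic treatment* has nurses record antithrombotic treatments with dates and says: "These data were collected to enable ascertainment of antithrombotic use current at randomisation". The risk score is fixed at baseline: "Only comorbidities noted in the medical record prior to the date of randomisation will be considered in the calculation of the CHADS2 score".

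**The concern.** The baseline value of an outcome is usually its strongest predictor, and adjusting for it is the cheapest gain in precision a trial can have. For the primary outcome the plan does this, since baseline anticoagulation is the baseline value of follow-up anticoagulation. The same variable is carried over to two outcomes that are scored differently. There it is only a partial stand-in, and for one risk group an inverse one.

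At stake are the width of the confidence intervals in the adjusted secondary analyses and the handling of chance imbalance. With about 40 practices per arm, the arms could differ by chance in baseline aspirin use at CHADS2 0 or 1. The listed covariates would not adjust for that, and the listed baseline comparisons would not show it.

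**Working it through.** **The plan's own figure.** This is for the primary outcome only. For 50% vs 60%, two-sided 5%, 80% power: [1.96√(2×0.55×0.45) + 0.842√(0.25+0.24)]² / 0.1² ≈ 387. The continuity correction brings this to about 407, as stated. The design effect is 1 + 24×0.04 = 1.96; 407×1.96 ≈ 798; 798/0.9 ≈ 887. These figures reproduce. No power is stated for the appropriateness outcomes, so the 80% used below is a reference point, not a claim of the plan.

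**Baseline anticoagulation against baseline appropriateness, by the protocol's rule.**

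| CHADS2 | Anticoagulant | Aspirin only | Neither | Relation |
|---|---|---|---|---|
| 2+ | appropriate | not | not | identical |
| 1 | appropriate | appropriate | not | the 'no' group is mixed |
| 0 | not | appropriate | not | reversed |

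**Assumptions (none in the documents).**
- CHADS2 0/1/2+ shares from 5/25/70% to 15/35/50%.
- Baseline anticoagulation 40/45/55% by CHADS2 group.
- 60% of the remainder on aspirin.
- A patient keeps the baseline treatment with probability 50% to 85%, and otherwise is redrawn from the same distribution.

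**Agreement of the two variables.** All patients agree at CHADS2 2+. At CHADS2 1 the share is 1 − 0.55×0.6 = 0.67. At CHADS2 0 it is 0.60×0.4 = 0.24. Overall: 0.70 + 0.25×0.67 + 0.05×0.24 = 0.88, down to 0.50 + 0.35×0.67 + 0.15×0.24 = 0.77.

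**Direction at CHADS2 0, 70% persistence.** Aspirin at baseline is 0.60×0.6 = 0.36.
- With baseline anticoagulation, follow-up appropriateness is 0.3×0.36 = 0.11.
- Without it: [0.36×(0.7+0.108) + 0.24×0.108]/0.60 = 0.53.

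A single anticoagulation main effect fitted to all patients (10/30/60% mix) is nevertheless positive, at about 0.5.

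**Precision, first outcome.** R² is from a linear fit on CHADS2 category plus the treatment variable. Power = Φ(2.80√[(1−R²planned)/(1−R²new)] − 1.96), clustering ignored.

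| Mix | Persistence | R² with anticoagulation | R² with appropriateness | Power if planned is 80% |
|---|---|---|---|---|
| 5/25/70 | 50% | 0.206 | 0.290 | 84.2% |
| 10/30/60 | 70% | 0.293 | 0.526 | 92.8% |
| 5/25/70 | 85% | 0.496 | 0.737 | 97.3% |

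Outside this range, at 2/15/83%, the result is 82.3%, 86.1% and 92.8% for 50%, 70% and 85% persistence.

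**Second outcome.** Assume further that 30% of warfarin users meet the INR criteria. Over three mixes and three persistence values, replacing anticoagulation by appropriateness gives about 82–88%, and using both gives about 83–93%. At 5/25/70% with 50% persistence, R² is 0.096 as planned, 0.138 replaced and 0.174 with both. Using both gives Φ(2.80√(0.904/0.826) − 1.96) ≈ 83.4%.

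**Clustering.** With ICC 0.04 and 25 patients per practice, the variance of a practice mean is proportional to 0.04 + 0.96/25 = 0.0784, of which 0.04/0.0784 = 51% lies between practices. Suppose the new covariate explains none of that part. In the 10/30/60%, 70% case the variance ratio is then 0.51 + 0.49×(0.474/0.707) = 0.84 and power is Φ(2.80/√0.84 − 1.96) ≈ 86%. The gain is about halved.

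**The case against.** The strongest reply is that nothing stated here is wrong. The list is a baseline-comparison list, and it becomes a covariate set only through the back-reference in *Statistical analysis*. The article gives no model formula and does not rule out outcome-specific covariates or a CHADS2-by-anticoagulation term, which a separate analysis plan could supply. This stands in part: the link is the natural reading, not an itemised one. But the article does point to a set of characteristics, and that set contains no aspirin or appropriateness variable, so no interaction among its members could separate aspirin users from untreated patients at CHADS2 1.

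The other limits also stand. At CHADS2 2+, 50–70% of patients under the assumed mixes, nothing is lost, and CHADS2 is itself listed. A reader might infer that the planned covariate points the wrong way in general, but the reversal is confined to CHADS2 0. A reader might also infer bias. The documents do not support that: practices are randomised and unadjusted analyses are planned as well.

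Finally, simply swapping anticoagulation for appropriateness would repeat the fault for the second outcome, because warfarin users there must also meet INR criteria. That objection is accepted, and both variables should be kept.

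**Conclusion.** The point holds as a minor, nearly free improvement to the adjusted analyses of two secondary outcomes. Baseline anticoagulation is the right covariate for the primary outcome, which is unaffected.

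The direction rests only on the protocol's scoring rule. The size rests on an assumed CHADS2 mix, aspirin share, treatment persistence and 80% reference power, and on patient-level linear R². Within the assumed range the first outcome gains about 4 points or more. The second gains less, by an amount that depends on how many warfarin users meet the INR criteria. A reader might take the larger figures as the gain to expect. The documents do not support this: they supply none of these inputs, and clustering could roughly halve the gain.

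**What to change.** In *Statistical analysis*, add one sentence. For the two appropriateness outcomes, the adjusted GEE model includes antithrombotic treatment appropriate at randomisation (yes/no), derived by the outcome's own stroke-risk rule from treatment current at randomisation, together with CHADS2 category (0, 1, 2+), and keeps baseline oral anticoagulation. Leave the primary-outcome model as it is. Add baseline appropriateness to the baseline-comparison list so that any imbalance is visible.

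The cost is one derived variable from records already audited and a sentence in each of two sections. No new data, patients or change to the sample size are needed.
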